### Sample size

Participants will be recruited from our prospective cohort. Based on our phase 1 cohort [14], we anticipated that the cohort of 50 SEEM patients, with duodenal samples collected by endoscopy, will include at least 20 without a single identified treatable infection, i.e. identified *Giardia* or *H. pylori* infection*.* The primary endpoint guiding our sample size estimate will be the anticipated differences in duodenal IFN_γ_ and APOA1 gene expression between subjects with EE and healthy controls. We anticipate that induction of IFN_γ_ gene expression will be associated with a reduction in APOA1 gene expression as per a recent study on Crohn’s disease [27] and that of Bragde et al. on celiac disease [28]. In the Crohn’s study, the mean (SD) Reads Per Kilobase per Million Mapped reads (RPKM) IFN_γ_ gene expression at diagnosis was equal to 1.86(2.7) in patients with Crohn’s, and 0.33(0.38) in healthy controls. The mean (SD) RPKM APOA1 gene expression at diagnosis was 927(1469) in patients with Crohn’s, and 3012(3080) in healthy controls. We anticipate similar differences between EE and healthy controls in our study. Based on these results, 30 healthy controls and 25 EE subjects without a specific treatable infection will provide 90% power to detect such a difference with α = 0.05. The secondary endpoint will be to perform an undirected analyses to capture the overall gene and signatures that are different between described groups. Based on previously published data for RNA-Seq samples size estimation [29], if we estimate a coefficient of variation of counts of 0.4 as was observed in 90% of the genes in a range of human studies, alpha of 0.05 and power of 0.8, a sample size of 20 per group will be needed.

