We will use a variety of computational/statistical approaches to assess the extent to which expression of various genes and their associated metabolic/signaling pathways in duodenal biopsies in children with celiac disease, Crohn’s disease, and EE overlap or differ. We will approach this using several statistical methods; PCA plots; Venn diagrams of the differently expressed genes between celiac disease vs. controls, EE vs. controls, and Crohn’s disease vs. controls; and associated pathway analyses. A significant overlap in pathways could provide insights into pathogenesis and new treatment approaches, such as tight junction modulation, which are in development for celiac disease [57]. Gene signatures distinct for EE would further provide a promising source of future therapeutic targets and initial tissue-level validation of promising biomarkers that would be useful for predicting growth and powering studies to test future interventions against EE. We also plan to compare proximal small intestinal duodenal biopsies with distal ileal biopsies in the Crohn’s cohort to determine how well the duodenal pattern of gene expression reflects the ileum.

Analyses of biopsies from both Crohn’s disease and celiac disease patients will also provide us the opportunity to test for the relationship between the microbial community and gene expression signatures. We will test for associations between taxa of the duodenal microbial community and specific clinical and gene expression metadata using Multivariate Analysis by Linear Models (MaAsLin) as has been described in prior studies [27, 49, 50]. A comprehensive description of this analysis method has been published online [58]. In short, for each arcsine square root transformed microbial feature, a model is selected from metadata using gradient boosting (gbm package [59]). Covariates in the selected model are then evaluated controlling for potential confounders using a general linear model. Additionally, confounders will also be assessed via construction of a causal pathway. Multiple comparisons over factor levels will be adjusted using a Bonferroni correction, and multiple hypothesis tests over all clades and metadata will be adjusted with a false discovery rate [60].

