All significant (α < 0.05) associations will be investigated in the analysis: clinical phenotype (including severity of wasting), stool and duodenal enteropathogen burden, endoscopic inflammation, histologic severity, and selected duodenal differentially expressed genes such as IFN_γ_ and APOA1. We plan to control for age, gender, and body mass index (as a measure of nutritional status) in our analysis. These analyses will identify specific duodenal microbial taxa associated with differences in IFN_γ_ and/or APOA1 gene expression across the three disorders tested; EE, Crohn’s disease, and celiac disease.

Next, analyses of mRNAseq performed on biopsy tissues will be carried out using polyA-RNA selection, fragmentation, cDNA synthesis, adaptor ligation, and library preparation with TRUSeq RNA Sample preparation (Illumina, San Diego, CA, USA). Paired-end 75 bp sequencing will be performed using the Illumina HiSeq 2000 in the CCHMC NIH-supported Digestive Health Center with a minimum depth of 20 million reads per sample. Reads will be aligned using TopHat [61]. The aligned reads will be quantified by Avadis NGS software (Version 1.3.0, Build 163,982 Strand Scientific Intelligence, Inc., San Francisco, CA, USA) using Hg19 as the reference genome and RPKM as an output. The DESeq algorithm will be used for RPKM normalization within Avadis NGS software. Two more recently applied alternative approaches for quantification will also be assessed using kallisto [62] and eXpress [63].

For RNA-Seq expression and gene enrichment analysis samples will be stratified into specific clinical subgroups including control, EE, celiac disease, and Crohn’s disease. For some analyses the EE group will be further sub-divided into those with an identified infection (e.g. *Giardia, H. pylori*) and those without an identified infectious etiology. In addition, we plan to stratify the Crohn’s patient samples by their location to assess expression differences between proximal (duodenal) and distal (ileum) small bowel expression.

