Other potential sub-stratification of the EE group will be based on CRP level, histologic severity, response to rotavirus infection (by measuring rotavirus IgA levels), and weight/height outcomes. Differentially expressed genes of the above stratified groups will be determined by the Audic Claverie method using the Benjamini-Hochberg false discovery rate correction (FDR 0.05) and analyzed for fold change differences. Normalized intensity values will be used for patterns of gene expression. Pearson correlation based on trend and rate of change will be performed for IFN_γ_ and APOA1 gene expression across defined groups for correlation coefficient of 0.98 < |r| < 1.

ToppGene [64], ToppCluster [65], and IPA (Ingenuity Systems) software will be used to test for functional annotation enrichment analyses of upstream regulators, immune cell types, pathways, phenotype, and biologic functions. Functional annotation enrichment analyses for immune cell type enrichments will be characterized using the Immunological Genome Project data series through ToppGene. Visualization of the functional networks will be obtained using Cytoscape v.3.02 [66].

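### The named differential-expression test leaves out between-child variance, so the stated FDR of 0.05 is not controlled for the genome-wide secondary endpoint

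*Protocol article*

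**What the plan says.** All quotes are from the protocol article.

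- **Test (Data analysis plan).** Differentially expressed genes of the stratified groups are "determined by the Audic Claverie method using the Benjamini-Hochberg false discovery rate correction (FDR 0.05") and then examined for fold-change differences. No fold-change cut-off is given.
- **Units compared (Data analysis plan).** For the RNA-Seq analysis, "samples will be stratified into specific clinical subgroups including control, EE, celiac disease, and Crohn’s disease", with further splits of the EE group.
- **Role of DESeq (Data analysis plan).** "The DESeq algorithm will be used for RPKM normalization within Avadis NGS software". It normalises and does not test. Kallisto and eXpress are named as alternatives for quantification only. No other differential-expression test appears.
- **Use of the lists (Data analysis plan).** They feed "Venn diagrams of the differently expressed genes between celiac disease vs. controls, EE vs. controls" and Crohn's disease v controls, and the associated pathway analyses.
- **Assumed variability (Sample size).** The genome-wide analysis is the secondary endpoint. It is sized with "if we estimate a coefficient of variation of counts of 0.4 as was observed in 90% of the genes", and with "alpha of 0.05 and power of 0.8, a sample size of 20 per group will be needed".
- **Group sizes and marker genes (Sample size).** "30 healthy controls and 25 EE subjects without a specific treatable infection will provide 90% power" for the primary comparison. IFN-gamma expression "was equal to 1.86(2.7) in patients with Crohn’s, and 0.33(0.38) in healthy controls"; APOA1 was 927 (1469) and 3012 (3080).

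**The concern.** Audic-Claverie gives the probability of a count in one library given the count in another, with both treated as Poisson. It has no replicate term. Applied to groups of children, it requires each group to be reduced to a single count, and the spread between children then plays no part in the p-value. The Benjamini-Hochberg step controls FDR only if the p-values fed into it are valid, so it cannot repair this.

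The article contradicts the test's assumption itself: the same endpoint is sized on a CV of 0.4. At stake are the gene lists behind the secondary endpoint, the overlap between EE, celiac disease and Crohn's disease, and the candidate targets and biomarkers to be drawn from them. The excess is largest in highly expressed genes. Such genes could recur in several disease-v-control lists and look like shared biology.

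**Working it through.** **Inputs from the article.** 30 controls and 25 EE children; CV 0.4; Benjamini-Hochberg at 0.05. The ratios of SD to mean for the marker genes are 2.7/1.86 = 1.45 and 0.38/0.33 = 1.15 for IFN-gamma, and 1469/927 = 1.58 and 3080/3012 = 1.02 for APOA1.

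**Assumptions (not in the article).** Mean counts, the share of genes truly changed, their fold change, equal library sizes, and how children are combined. Two ways of combining are tried: summed counts, and group averages entered as two libraries.

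**1. The plan's own figures.**
- *FDR 0.05.* With no between-child variance (CV 0), Audic-Claverie on summed counts gives a simulated FDR of about 0.045-0.048 (10% of genes changed 1.5-fold). The procedure works when its assumption holds.
- *n = 20 per group.* Fold change and mean count are not stated. With an assumed fold change of 1.5 and mean count of 20, n = 2(1.96 + 0.84)²(1/20 + 0.4²)/(ln 1.5)² = 20.1. In that formula 0.16 of the 0.21 variance term is the between-subject part, which the test omits.

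**2. Null genes, summed counts.** For a mean count μ per child, the true variance of a count is μ + 0.16μ², whereas the test uses μ. The ratio is 1 + 0.16μ and does not depend on the number of children. The rejection rate at nominal 0.05 is 2Φ(−1.96/√(1 + 0.16μ)):

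| μ | variance ratio | rejection rate |
|---|---|---|
| 10 | 2.6 | 0.22 |
| 100 | 17 | 0.63 |
| 1000 | 161 | 0.88 |

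**3. Null genes, group averages.** The test assumes variance 2μ. The true variance is (1/30 + 1/25)(μ + 0.16μ²), so the ratio is 0.0367(1 + 0.16μ). This equals 1 at μ ≈ 164. Below that the test is conservative; above it the test rejects too often. At μ = 1000 the ratio is 5.9 and the rejection rate is 2Φ(−1.96/√5.9) ≈ 0.42.

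**4. Realised FDR after Benjamini-Hochberg.** Simulation of 15,000 genes with gamma-Poisson counts, log-normal gene means (log-SD 1.3), 30 v 25 children, CV 0.4, 10% of genes changed 1.5-fold, no fold-change filter:

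| Median count | Summed | Averaged | Replicate-based t-test on log counts |
|---|---|---|---|
| 20 | 0.74 | 0.10 | 0.04 |
| 100 | 0.84 | 0.39 | 0.04 |
| 500 | 0.88 | 0.68 | 0.05 |

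**5. Sensitivity (median counts 20-500).**
- CV 0.2: 0.49-0.85 summed; 0.00, 0.05 and 0.34 averaged.
- CV 0.4, 30% of genes changed 2-fold: 0.42-0.65 summed; 0.02-0.36 averaged.
- CV 0.4, 10% changed 1.5-fold, with an assumed 1.5-fold cut-off: 0.09 or less summed; 0.005 or less averaged. With a 1.25-fold cut-off: 0.28-0.41 and 0.05-0.24.
- CV 1.0, 10% changed 1.5-fold, 1.5-fold cut-off: 0.71-0.74 summed; 0.62-0.71 averaged. With 30% changed 2-fold: 0.28-0.30 and 0.17-0.27.

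**The case against.** A reader might infer that most genes declared significant would be noise. The article does not support that as a general statement, for three reasons.

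- **Combination is not stated.** RPKM output and normalised values fit group averages at least as well as summed raw counts. On averages the excess is much smaller at low counts or low CV, and in some settings realised FDR is below 0.05. This stands, and it is why the size is given as a range. It does not rescue the plan: averaging is conservative for some genes and anti-conservative for others, so a result below 0.05 depends on where the counts happen to lie.
- **There is a fold-change step.** The same sentence goes on to fold changes, and at CV 0.4 an assumed 1.5-fold filter would remove most of the excess. This stands as a conditional point. No cut-off is stated, a 1.25-fold filter leaves a clear excess on summed counts and in most averaged settings, and at a CV of 1.0, close to the lowest of the article's four marker-gene ratios, a 1.5-fold filter does not restore control.
- **One CV for all genes is a simplification.** This is true, and results move in both directions with it.

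A reader might also extend the defect to the primary endpoint. No test is named for the IFN-gamma/APOA1 comparison, so that is not shown. Nor does the article say that duodenal and ileal Crohn's samples come from the same patients, so a failure to respect pairing cannot be asserted. Direct EE v celiac and EE v Crohn's contrasts are a design preference and no part of this point. Finally, the affected outputs are exploratory and can be corrected at analysis. That limits the consequences, but an FDR of 0.05 is still stated and not delivered.

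**Conclusion.** Wrong as written. The only differential-expression test named omits a source of variance that the article itself assumes, so FDR 0.05 is not controlled for the genome-wide secondary endpoint or for the Venn and pathway results built on it. That conclusion follows from the definition of the test and the stated CV.

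The size is less certain. At CV 0.4, with 10% of genes changed 1.5-fold and no filter, realised FDR is about 0.74-0.88 on summed counts and 0.1-0.7 on averages. These figures rest on assumed counts, effect sizes and share of changed genes, and on one of two unstated ways of combining children. With a smaller CV, more or larger true changes, or a fold-change cut-off at moderate CV, the excess is smaller. At CV near 1 it remains about 0.6-0.7 even after a 1.5-fold cut-off, if 10% of genes are changed 1.5-fold.

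**What to change.** Replace Audic-Claverie with a test that estimates between-child dispersion on raw or estimated counts: a negative-binomial model (DESeq2 or edgeR), or limma-voom. Include age and sex as covariates, and block on patient where duodenal and ileal samples come from the same child. Keep Benjamini-Hochberg at 0.05. If a fold-change cut-off is part of the definition of a differentially expressed gene, state its value.

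The cost is a change of wording; no new samples or sequencing are needed. Fewer genes will be called. In a simulation with median count 200 (log-SD 1.5), CV 0.4 and 10% of genes changed 1.5-fold, a replicate-based t-test with Benjamini-Hochberg at 0.05 had power 0.65 with 30 v 25 children and 0.39 with 20 v 20. Audic-Claverie on summed counts appeared to reach 0.99 in the same setting, but at a realised FDR of 0.86.

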**Table 3 Tab3:**
[figure not shown]
Plan of biopsy work up on children selected for UGI endoscopy

Because UGI endoscopies are rarely performed in children under 2 in Pakistan and due to ethical and cultural considerations, it is not possible to obtain duodenal biopsies from national healthy children that could serve as a control in our analysis. This is one of the major limitations of our study and as the results from Campbell et al. [10] support the utility of healthy age-matched children from high-income countries for identifying key gut pathogenic pathways in low-income settings, we are proposing to use age-matched controls from the United States for comparison.

Therefore, we plan to enroll 3 different control groups, all comprising of children under the age of 11 years, with a preference to enroll children under the age of 5 years. Our first control group will comprise of 30 healthy children, who will undergo endoscopy at CCHMC as part of a diagnostic workup for digestive symptoms, but whose biopsies and diagnoses are not supportive of eosinophilic esophagitis, celiac disease, or inflammatory bowel disease, and who were not treated with antibiotics ≤4 weeks prior to endoscopy.

As EE and celiac disease share some shared histopathological features [24, 25], we will focus on celiac disease as an enteropathy control group. We plan to enroll 30 children with newly diagnosed celiac disease per endoscopy at CCHMC to assess the extent to which gene signatures and associated biologic pathways for children with celiac disease or EE overlap or differ. Lastly, while we recognize that duodenal and ileal histopathology in the majority of Crohn’s cases differ from celiac disease and EE, the differentially expressed ileal gene signature in Crohn’s patients bears remarkable similarities to individual gene expression patterns reported for EE [10, 26], i.e. induction of IFN_γ_, REG1B. Therefore, our third control group will be 30 children with newly diagnosed Crohn’s disease per endoscopy at CCHMC.

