For those children who fail to respond to nutritional rehabilitation and in whom no apparent cause of malnutrition can be identified after basic laboratory workup, we will conduct a more thorough investigation to identify the cause of undernutrition. It is important to note that this nutritional rehabilitation program is immensely supervised, with study staff allowed to visit homes more than once a week to ensure compliance if required. Additionally, our Phase 1 study had a 90.5% compliance for nutritional intervention, and we will therefore be able to identify which children fail to respond to rehabilitation due to biological reasons vs the unlikely event of failing due to a lack of compliance. If the child remains at WHZ < − 2 despite all the above interventions, then s/he will undergo medical evaluation (including a core standardized laboratory panel which includes celiac screening, complete blood count, complete metabolic panel, international normalized ratio, erythrocyte sedimentation rate, and C-reactive protein, additionally, the pediatric gastroenterologist will not be limited to this panel and may order any additional tests as clinically indicated) to assess if there is a clinical indication for further workup to identify a secondary cause of the malnutrition, including UGI endoscopy at AKUH. Diagnostic evaluation, including the UGI endoscopy, will be used to guide further management. For example, dietary management of celiac disease counseling (i.e. initiation of gluten free diet [31]), will be provided to the families of affected children in the local language, and identified infections will be treated according to the standard of care (as was performed in our Phase 1 study for n = 1 child diagnosed with celiac disease [14]). Follow-up will be continued to facilitate treatment and ensure the best possible outcomes depending on the pathology identified.

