Lastly, an anticipated challenge in interpreting clinical biopsies from EE and celiac disease will be the possible histopathological overlap between these distinct but related enteropathies [10, 22]. In light of this, we propose to use duodenal biopsy data (converted to whole slide images using Leica SCN400 slide scanner [Meyer Instruments, Houston, TX] and Olympus VS120 Virtual Slide Microscope [Olympus Corporation Inc., Center Valley, Pennsylvania]) from EE, celiac disease and normal healthy biopsy from patients recruited in SEEM and archival duodenal biopsies from the UVa BTRF as data input for a deep learning image analysis algorithm. Deep learning, or machine learning, has been said to be the natural extension to our current statistical analysis [67] especially in the context of multiomic data as in SEEM, and is at the forefront of advances in both technology and medicine [68]. We will use a subtype of deep learning known as Convolutional Neural Networks (CNNs) [69], to detect morphological distinguishing histological features between disease phenotypes. We will also couple our CNN layers with a deconvolution layer [70, 71], and a Gradient Class Activation Map layer [72], which will allow us to trace back high activation features to the corresponding biopsy. This will allow us to enhance the detection of pathologic morphological features that can help distinguish between celiac disease and EE, both when compared to each other and also when compared to healthy duodenal tissue. Furthermore, in addition to applying the EEDBI scoring system, we will use this deep learning driven approach to correlate high activation features to identify multiomic patterns not identified by traditional pathology scoring.

The overall schedule for enrolment, interventions and assessments, including UGI endoscopy and biopsies, is described in Fig. 3; and the data transfer between each collaborating institution is outlined in Fig. 4. To ensure optimal outcomes from this ambitious undertaking, we designed SEEM with monitoring and quality control measures, timelines for milestones, anticipation of challenges, and consideration of ethics and data dissemination.

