Additionally, several questions arose in the development and implementation of our Phase 1 EE study and subsequently in SEEM, all of which were reviewed by the Ethical Review Committee (ERC) at AKUH for discussion and resolution. For example, adverse events that may arise during endoscopy were a major concern; to mitigate issues, investigators have developed a priori definitions, assessment criteria and action guidelines including an overnight stay in Karachi prior to return to the subject’s village Matiari. Endoscopy of eligible children will be performed at the AKUH (accredited by the Joint Commission International, IL, USA since July 2006 [74, 75]) where the highest safety standards at par with hospitals in high-income country settings are met including access to a pediatric intensive care unit, pediatric surgeons and dedicated clinical dieticians. Of note, children who fail to respond to nutritional rehabilitation are evaluated by a team of physicians including a trained pediatric gastroenterologist (KS). A qualified anesthetist attends every endoscopy procedure to assess and administer steps as required for sedation. The participant’s oxygen saturation level, pulse rate and blood pressure are continuously monitored throughout the procedure. Resuscitation measures and complete pediatric Intensive Care Unit (ICU) support remain available during the procedure for immediate resuscitation if necessary. Clinical findings from the biopsies (e.g. presence of gastritis, H pylori infection, Giardiasis or diagnosis of celiac disease) are made available as soon as possible so that appropriate treatment can be undertaken. Additionally, morbidity and poor appetite also represent a big challenge; by providing close follow-up, proper counseling and by practicing supportive feeding techniques, this issue can be resolved. Our field team in Matiari is led by two physicians registered by the Pakistan Medical and Dental Council (PMDC), who will oversee these challenges, along with access to a panel of North American trained pediatric subspecialists ([name] - pediatric infectious disease; KS, SS, and [name] - pediatric gastroenterology) for additional expertise as needed.

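### In the image analysis EE is confounded with country, so CNN features separating EE from normal or celiac tissue cannot be read as morphology from these slides alone

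*Protocol article*

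**What the plan says.** **Input and purpose.** The last part of the Data analysis plan describes the CNN. Besides EE slides, it takes "celiac disease and normal healthy biopsy from patients recruited in SEEM and archival duodenal biopsies from the UVa BTRF as data input". Slides are "converted to whole slide images using Leica SCN400 slide scanner" or on a second instrument, an Olympus VS120; the text does not say which slides go on which. The aim is to detect features that "help distinguish between celiac disease and EE, both when compared to each other and also when compared to healthy duodenal tissue". Activation maps trace these features back to the tissue, and the features are then used to find multi-omic patterns that pathology scoring misses.

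**Where each class comes from.**
- EE: children who do not respond to nutritional rehabilitation are assessed for "further workup to identify a secondary cause of the malnutrition, including UGI endoscopy at AKUH". The safety section repeats this: "Endoscopy of eligible children will be performed at the AKUH". Sample size expects "the cohort of 50 SEEM patients, with duodenal samples collected by endoscopy".
- Normal: Study settings and participants states that "it is not possible to obtain duodenal biopsies from national healthy children that could serve as a control in our analysis", so 30 controls with no supporting diagnosis are endoscoped at CCHMC.
- Celiac: the planned group is 30 children with "newly diagnosed celiac disease per endoscopy at CCHMC".
- Archive: the UVa slides come from a US institution; their number and diagnoses are not given.

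**The concern.** If one class comes only from one country, whatever else differs consistently between the countries also identifies that class. This includes tissue handling, but also the patients: US controls may be up to 11 years old, with a preference for under 5, whereas the Pakistani cohort is followed from birth to 2 years. A network that learned only such a difference would look excellent. Cross-validation within the same slides would not expose it, because the difference is present in every fold.

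Activation maps do not settle the matter. They show where the network responds. Hue, section thickness or texture is present in villi and crypts too, so a map can point at plausible tissue while a processing signal drives the decision.

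At stake is the purpose given for this analysis, which is to resolve the histological overlap between EE and celiac disease. A country difference could be reported as EE morphology and then carried into the multi-omic results as pathology that conventional scoring had missed.

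**Working it through.** The article gives no sample size or accuracy for the image classifier, so there is no figure to reproduce. The check asks how well a rule that knows only the country would do: call a slide EE if it is Pakistani and not EE if it is from the USA.

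**Inputs.** 50 Pakistani endoscopies (Sample size); 30 celiac and 30 normal controls at CCHMC (Study settings and participants). Let *k* be the number of celiac cases among the 50. *k* is not given, so it is varied. Assumptions: one slide per child, the other 50 − *k* children count as EE, and the UVa archive is left out because its labels are unknown.

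| Source | EE | Celiac | Normal |
|---|---|---|---|
| AKUH, Pakistan | 50 − k | k | 0 |
| CCHMC, USA | 0 | 30 | 30 |

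**EE v normal.** All 50 − *k* EE slides and all 30 normal slides are classified correctly: (80 − *k*)/(80 − *k*) = 100% for every *k*.

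**EE v celiac.** Correct are the 50 − *k* EE slides and the 30 US celiac slides, out of 80: accuracy = (80 − *k*)/80. Balanced accuracy is the mean of 100% (EE) and 30/(30 + *k*) (celiac).

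| k | Accuracy | Balanced accuracy |
|---|---|---|
| 0 | 80/80 = 100% | 100% |
| 1 | 79/80 = 98.8% | 98.4% |
| 5 | 75/80 = 93.8% | 92.9% |
| 10 | 70/80 = 87.5% | 87.5% |
| 20 | 60/80 = 75.0% | 80.0% |

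**Celiac v normal within CCHMC.** Both groups are from one site, so country carries no information: 30/60 = 50%.

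**Plausible k.** The article reports one celiac diagnosis in Phase 1, and 11 Phase 1 endoscopies. If that child was among the 11 (an assumption), the rate is 1/11 = 9.1%, with a 95% Clopper-Pearson interval of 0.2% to 41%. In 50 endoscopies this means 50 × 0.091 = 4.5 expected cases, range 0.1 to 20.6.

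**Archive.** If the UVa slides are celiac or normal, they join the US non-EE cells. The country rule then stays at 100% for EE v normal and rises for EE v celiac.

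**Reading.** For EE v normal no network can beat the country-only rule, so no accuracy on these slides can show that morphology was used. For EE v celiac the same holds at *k* = 0. At the central estimate of about five cases the country-only rule still reaches about 94%.

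**The case against.** **It is a condensed article.** Stain normalisation and validation are commonly left to a full protocol or analysis plan, and their absence here is not a defect. That stands. The point does not rest on it: the article itself fixes which class comes from which country and states the inference to be drawn. No later modelling detail changes the first.

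**The limitation is admitted and other evidence is planned.** The lack of local healthy biopsies is called a major limitation, the consortium's pathologist score is applied as well, and the Discussion promises comparison with other biopsy-based EE studies. This softens the consequence. However, the image analysis paragraph does not carry the limitation over, and it seeks patterns beyond the pathologist score.

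**Stronger readings a reader might infer.**
- *Diagnosis is completely aliased with site.* Not supported. Pakistani children are screened for celiac disease and one was diagnosed in Phase 1, so some Pakistani celiac slides are possible. Celiac v normal is not aliased within CCHMC.
- *Two scanners split the diagnoses.* Not supported. No allocation of slides to scanners is stated.
- *Fixation, staining and sectioning differ by class.* Not stated either. Biopsies are handled under standard operating procedures for this protocol, some immunohistochemistry goes through UVa, and Table 3 and Figure 4 are not visible here. Central staining or scanning cannot be excluded. It would not, however, remove differences that arise before slides reach a central laboratory, or the age difference.

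**Conclusion.** The concern holds for two of the three contrasts. EE v normal is fully confounded with country. EE v celiac is fully or nearly so: country alone gives 100% with no Pakistani celiac case, 98.8% with one and 87.5% with ten. Only near the upper end of the very wide Phase 1 interval, at about 20 cases, does it fall to 75%. Celiac v normal within CCHMC is not confounded.

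The article's reading of activations as distinguishing morphology is therefore not supported by these slides for the EE contrasts. This does not show that the network would use a processing signal, only that the design cannot tell the two explanations apart. The figures rest on the planned numbers, one slide per child, and all Pakistani non-celiac endoscopies counting as EE. The point is worth acting on before the image analysis is run, but it concerns that analysis only.

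**What to change.** 1. Scan all slides on one of the two named scanners, with EE, celiac and normal slides interleaved.
2. Apply stain and colour normalisation before training, with a greyscale run as a sensitivity analysis.
3. Report the country-only baseline accuracy beside the CNN accuracy for each contrast.
4. Check the predictions on any Pakistani celiac or other non-EE slides, kept out of training, and, if available, on EE slides from the consortium's Zambia and Bangladesh cohorts. Few Pakistani slides will give an imprecise answer. Success on the other cohorts would speak against an AKUH-specific signal, though not against every difference from US laboratories.
5. State that features separating EE from celiac or normal tissue are confounded with site and are exploratory unless confirmed by such a check, and carry that label into the multi-omic correlations.

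A comparison of CCHMC with UVa slides within one diagnosis should not serve as the decision rule. Both are US sites, so it cannot detect a signature specific to AKUH and could reassure falsely.

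Steps 1 to 3 reduce or expose a processing signal but do not remove the confounding; steps 4 and 5 decide what may be claimed. The cost is some re-scanning and computing, possibly a lower accuracy, and a narrower claim. No new biopsies or readers are needed.
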